### Interim analyses {21b}

No interim analyses are planned due to the low-risk nature of the study.

### Methods for additional analyses (e.g., subgroup analyses) {20b}

No subgroup analyses will be performed.

### Methods in analysis to handle protocol non-adherence and any statistical methods to handle missing data {20c}

We anticipate missing data at random (MAR), where missingness will not depend on the unobserved data but conditional to the observed data. We shall use observed data to impute missing values for patients with missing data. Multiple imputations will be employed to take uncertainty into account by replacing each missing value with a set of possible values to create multiple imputed values. The number of imputations will be determined by the percentage drop out rate. In this study, we anticipate a 10% drop out; therefore, we are planning 10 imputations. We shall perform sensitivity analysis that will weaken the missing data assumption to assess departures in the primary analysis.

### Plans to give access to the full protocol, participant-level data, and statistical code {31c}

Access to the full protocol, participant-level data, and statistical code will only be possible through authorization by the principal investigator.

## Oversight and monitoring

### Composition of the coordinating center and trial steering committee {5d}

The study coordinating center is at Mengo Hospital. The coordinating center comprised the principal investigator, study coordinator, and data entry assistant. The principal investigator and the study coordinator have created the study trial manual and have established the data collection processes including the standard operating procedures. The principal investigator working in conjunction with the other authors ([name]) was charged with the conception of the research question and developed the proposal which was submitted for approval. The principal investigator and study coordinator trained study nurses and provide routine communication to the study health facilities. The study coordinator is in charge of routine communication with the study facilities. The study coordinator prepares the monthly progress report to the Mengo Hospital Ethics Committee. The principal investigator, study coordinator, and data entry assistant are responsible for the data oversight. The study coordinator is in charge of logistical provision to the study facilities. The PI and study coordinator work in conjunction with the study nurses to monitor and report adverse events. An independent trial steering committee to oversee the trial has been formed. The Trial Steering Committee comprised an independent epidemiologist, diabetologist, cardiologist, biostatistician, principal investigator, and study coordinator. The independent trial steering committee oversees the trial. Study nurses identify and recruit potential participants and guide them through the consenting process. The Trial Steering Committee (TSC) meets every after 2 months during the trial. The trial does not have stake holder and public involvement group (SPIG).

### Composition of the data monitoring committee, its role, and reporting structure {21a}

The data will be monitored by the team from the coordinating center.

### Adverse event reporting and harms {22}

The study is largely a low-risk one. However, in case of any adverse event or harm, the study participants will be required to inform the study nurse immediately. If the patient develops an AE, he or she will be discontinued from the study. The study nurse will record the event and will follow the study standard operating procedures on the management of adverse events and harms. The serious adverse event will be reported to the coordinating center in Mengo Hospital.

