### Coaching intervention

The second component of the intervention will be the coaching support where individual participants in the intervention group will be given support at home. The study nurses will make individualized telephone calls, send text messages, and operate a 24-h mobile telephone service to answer study participants’ questions and concerns. The phone calls will be structured along the health education topics provided at the health facility. It is anticipated that telephone calls will last for 7 min per participant. Thus, for 194 participants, 22 h of calls will be consumed each time the study participants are called. Participants will be called 3 times during the entire trial period. The participant and the areas discussed will be registered in the call log. Text messages will be sent every after 2 months. The messages will contain topics discussed during the health education talks and in the leaflet. Every time messages are sent, they will be recorded in the text messages’ log.

The telephone calls and text messages will reinforce individualized hypertension and ASCVD management plan at home. The nurse-patient relationship which is key in the chronic disease care model will be strengthened through calls and text messages. The intervention components are as shown in Fig. 4.

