### The usual hypertension/ASCVD care

The control group of the study will comprise the usual care that is the doctor- or clinical officer-led at health centers IV and higher where either patients are referred by nurses or refer themselves with symptoms of ASCVD. In the usual care, patients with diabetes are not subjected to ASCVD risk quantification. Nurses give general health education on diabetes self-care practice which is not structured along with primary hypertension and ASCVD prevention and management. Health education does not build a nurse-patient relationship with a well-educated motivated patient at the center. All patients are given the same management package irrespective of their risk factor profile. Management of hypertension and ASCVD in the health facilities in Uganda is not protocol-based as every facility manages diabetes and hypertension differently. Apart from the general Information Education Communication materials at the clinics, patients are not given information leaflets and are not followed with phone calls and text messages and neither can they call the health workers any time of the day. Patients are followed only in the clinics when they are given review appointments by the doctors or clinical officers. Nurses in these facilities have varied training and skill in diabetes management.

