### Criteria for discontinuing or modifying allocated interventions {11b}

Given the fact that the intervention components are some of the routine procedures at the clinics, we anticipate low risk. However, if a participant opts out, or develops an adverse event, she or he will be discontinued from the study.

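### Self-reported adverse events, unequal nurse contact and discontinuation after an event can make recorded harms and loss of 6-month SBP differ by arm through ascertainment alone

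*Protocol article*

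**What the plan says.** **Detection.** Adverse event reporting and harms {22} states that, when an AE or harm occurs, "the study participants will be required to inform the study nurse immediately". The nurse then records the event. The oversight section {5d} adds that the coordinating centre and nurses monitor and report AEs, but gives no method.

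**Consequence.** The same section continues: "If the patient develops an AE, he or she will be discontinued from the study". The discontinuation criteria {11b} agree: "if a participant opts out, or develops an adverse event, she or he will be discontinued from the study". Neither sentence sets a severity threshold or says whether outcome measurement continues.

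**Contact, intervention arm.** Coaching intervention: "The study nurses will make individualized telephone calls, send text messages, and operate a 24-h mobile telephone service to answer study participants’ questions and concerns", and "Participants will be called 3 times during the entire trial period". The intervention description adds group education every 2 months for 6 months, each session followed by 15 minutes of questions.

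**Contact, control arm.** The usual hypertension/ASCVD care section says that patients receive no follow-up calls or texts, "neither can they call the health workers any time of the day", and are followed only at clinic review appointments.

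**Other relevant text.** Participants and study nurses are unblinded {17a}. The single follow-up assessment is at 6 months, and AE enquiry is not among its listed measurements ({18a}, Table 1). Analysis is by ITT {20a}. Missing data are to be multiply imputed under missing at random (MAR), with a sensitivity analysis that relaxes the assumption {20c}.

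**The concern.** The duty to report is the same in both arms, but the occasions and means to report are not. An intervention participant speaks to a study nurse on a schedule and can reach one at any hour. A control participant has to raise the event at a review or find another way. More AEs could be recorded in the intervention arm simply because there are more chances to mention them.

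Two things are at stake. First, the intervention has nurses start and manage antihypertensive and lipid-lowering treatment under a protocol, and the results are meant to inform task-shifting policy. A count of AEs by arm would be hard to read in either direction: an excess could be ascertainment, and a real excess could be dismissed as ascertainment. Second, because a recorded AE leads to discontinuation from the study, unequal recording can become unequal loss of the primary outcome.

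**Working it through.** **1. The arms side by side**

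| | Intervention | Usual care |
|---|---|---|
| Coaching calls | 3 | none |
| Texts | every 2 months | none |
| 24-h line to nurses | yes | no |
| Structured group sessions | every 2 months | none (general education only) |
| Other routine contact | care from study nurses | clinic reviews |
| 6-month study visit | yes | yes |
| Stated AE route | participant informs nurse | participant informs nurse |

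The 6-month visit is the one scheduled follow-up assessment common to both arms, and no AE question is listed for it.

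**2. The plan's own sample size, as a base** (Sample size {14})

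- Mean variance: (17.2² + 18.7²)/2 = 322.8.
- Individually randomised n per arm: 2 × 322.8 × (1.96 + 0.84)²/8.5² ≈ 70.1.
- With k = 4 clusters per arm and ICC 0.035, cluster size m = n(1 − ICC)/(k − n × ICC) = 70.1 × 0.965/(4 − 70.1 × 0.035) ≈ 43.8, or 175.1 per arm (174.3 with n = 70). The plan states 174, so it is reproduced within rounding.
- Loss to follow-up: 174/0.9 = 193.3, rounded to 194. The allowance for all losses is 10% of 194 = 19.4 per arm, with nothing separate for AE-triggered discontinuation.

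**3. Spurious gap in recorded AEs (assumed rates)**

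The documents give neither an AE risk nor a capture rate. Assume the same true risk r in both arms, capture of 90% in the intervention arm and 30–70% in control. Recorded events = 194 × r × capture; gap = r × (0.90 − control capture).

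| True risk | Intervention | Control (30% to 70% capture) | Gap, percentage points |
|---|---|---|---|
| 5% | 8.7 | 2.9 to 6.8 | 3 to 1 |
| 10% | 17.5 | 5.8 to 13.6 | 6 to 2 |
| 20% | 34.9 | 11.6 to 27.2 | 12 to 4 |

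With equal capture the gap is 0 at every risk.

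**4. Carry-over to the primary outcome**

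If discontinuation ends outcome collection, the counts in step 3 are also losses of the 6-month SBP. Against the allowance of 19.4, the intervention arm would use 8.7, 17.5 or 34.9. There is no intermediate SBP assessment, so a discontinued participant contributes only a baseline value. If the rule is followed literally, nobody with a recorded AE has a 6-month SBP. The imputation model then has to predict their values from participants without a recorded AE.

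**5. Effect on power**

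SE² = 17.2²/n₁ × [1 + (n₁/4 − 1) × 0.035] + 18.7²/n₂ × [1 + (n₂/4 − 1) × 0.035]; power = Φ(8.5/SE − 1.96), with n₁ intervention and n₂ control participants analysed.

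- 174 v 174: SE = 3.04, power 79.9%.
- 155 v 174 (about a further 10% of 194 lost): SE = 3.07, power 79.0%.
- 136 v 174 (about a further 20% of 194 lost): SE = 3.11, power 78.0%.

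The concern is therefore possible bias, not sample size.

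**The case against.** The case on the other side has real force.

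- **Other routes may exist.** A reader might infer that AEs are collected only when a participant makes contact. The protocol does not say so. Section {5d} mentions AE monitoring, and operating procedures that are not shown may contain a form. This stands: self-report is the only route described, not demonstrably the only one used. However, {22} cites those procedures for managing events, not for detecting them.
- **Control participants are not cut off.** A reader might infer that they cannot call at all. The text denies only calls at any time of day. The retention section {18b} also promises periodical calls without naming an arm, although {11c} describes its calls as part of the intervention's motivation component, and the usual-care section says that patients are not followed with calls. Even on the generous reading, those calls are for retention and not AE enquiry.
- **No between-arm harms analysis is planned.** That is correct, so no stated analysis is invalidated. The point concerns any by-arm harms summary that is later reported.
- **Unequal loss does not by itself bias the SBP difference.** This also stands. Bias needs missingness related to SBP beyond what is observed, and {20c} plans imputation and a sensitivity analysis. These soften the problem, but they cannot recover measurements that the protocol's own rule may stop.
- **The figures are driven by their assumptions.** They are. For example, a doubling of recorded AEs under 80% v 40% capture is just the ratio of the two assumed rates and is no evidence of its size.

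**Conclusion.** The concern holds as a possibility built into the stated procedures: recorded AEs can differ by arm through ascertainment alone. Because {11b} and {22} discontinue a participant with an AE, that difference can pass into unequal loss of the 6-month SBP, in tension with the ITT statement in {20a}.

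The size cannot be determined from the documents. Under the assumptions of equal true risk of 5–20%, 90% capture in the intervention arm and 30–70% in control, the gap is about 1–12 percentage points; under equal capture it is zero. The carry-over depends on whether discontinuation ends outcome measurement, which the text leaves open. Power would fall by no more than about 2 points in the cases checked.

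A reader might go further and conclude that harms will differ, or that the primary comparison is biased. The documents do not support either: they give no AE or capture rates, and they show no link between AE-triggered loss and SBP beyond the observed data. The point merits a change because the repair is cheap, not because damage is proven.

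**What to change.** 1. At the existing 6-month visit, ask every participant in both arms the same short structured questions on AEs and hospitalisation. Base any by-arm harms summary on those answers, and list spontaneously reported events separately. The cost is one form page in both arms and some recall error over 6 months; no extra visit is needed.
2. Reconcile the AE discontinuation sentences in {11b} and {22} with ITT in {20a}. State whether discontinuation from the study ends outcome follow-up, so that the 6-month SBP is still collected for the ITT analysis where the participant consents. This concerns data collection only; what happens to a participant's care after an AE is for the trial's clinicians. The cost is a sentence or two in the protocol, plus keeping these participants on the 6-month visit list.
3. Reconcile the periodical calls in {18b}, which name no arm, with {11c} and the usual-care section, so that it is clear which contacts the control arm receives.

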### Frequency and plans for auditing trial conduct {23}

We have no plans for independent trial auditing.

### Plans for communicating important protocol amendments to relevant parties (e.g., trial participants, ethical committees) {25}

Any protocol amendments that may affect the study design or conduct and patient safety will be submitted to the Mengo Hospital Research Ethics Committee for approval. If approved, this will be communicated to the Uganda National Council of Science and Technology and the study health facilities. The Pan African Trial Registry and the journal publishing the protocol will be appropriately informed.

## Dissemination plans {31a}

We will disseminate the findings from this trial through peer-reviewed publications and local and international scientific meetings. A project report written in non-technical language will be sent to all participants.

## Discussion

Atherosclerotic cardiovascular disease (ASCVD) is a leading cause of morbidity and mortality among patients with type 2 diabetes in Uganda. Hypertension which is a major contributor to ASCVD is highly prevalent, undiagnosed, and poorly controlled. One of the reasons for poor control of hypertension and ASCVD in the primary care setting is the scarcity of doctors [13]. Nurses are readily available and spend more time with the patients and are traditionally well versed in self-care and administration of systematic educational interventions [27]. Thus, there is a need to shift the task of management of hypertension and ASCVD from doctors to nurses. However, there is a paucity of data on nurse-led hypertension management among patients with type 2 diabetes in our setting. To the best of our knowledge, this is the first trial in Uganda that examines the effect of a nurse-led lifestyle choice and coaching intervention on systolic blood pressure among patients with type 2 diabetes with a high ASCVD risk. The intervention is based on Wagner’s chronic care model that has been extensively studied in diabetes care. We believe findings from this trial will be useful in drafting national guidelines on the management of hypertension and ASCVD among patients with type 2 diabetes.

## Trial status

Protocol version 03, 2021 January 19

Recruitment is planned to start on 28 December 2020 and is expected to last for 6 months until 1 July 2021.

## Abbreviations

PACTR: Pan African Trials Registry
ASCVD: Atherosclerotic cardiovascular disease
NHANES: National Health and National Survey
UKPDS: United Kingdom Prospective Diabetes Study
HOT: Hypertension Optimal Treatment
SHEP: Systolic Hypertension in the Elderly Program
Syst-Eur: Systolic Hypertension in Europe
CCM: Chronic care model
SPIRIT: Standard Protocol Items Recommendations for Intervention Trial
ICC: Intracluster correlation coefficient
BMI: Body mass index
WC: Waist circumference
HC: Hip circumference
WHR: Waist to hip ratio
WHtr: Waist to height ratio
HPLC: High-performance liquid chromatography
HbA1C: Glycated hemoglobin
DCCT: Diabetes Control and Complications Trial
ITT: Intention-to-treat
ANCOVA: Analysis of covariance
